## Abstract

The EISI study protocol aims to address the low participation rate in physical exercise programs among older individuals, emphasizing its significance as a non-pharmacological therapeutic approach for overall health and increased physical activity. The objectives include implementing physical activity (PA) and educational health programs in Jequié, Bahia, Brazil, targeting the Family Health Strategy population to enhance local physical activity levels among older individuals. The study also seeks to evaluate the program's feasibility, safety, and sustainability for large-scale implementation, along with assessing its impact on immune and inflammatory response biomarkers to the SARS-CoV virus, as well as physical-functional and brain health. Participants, aged 60 or above, will be divided into two groups: multicomponent exercise (MCE) and behavioral change interventions (BCI). The study employs a mixed-method approach, utilizing a non-randomized controlled short-term pathway model for a 4–8 weeks of pilot study and 16-week intervention impact assessment. Data collection encompasses various aspects such as sociodemographic information, mental health, physical fitness, fall risk, functional capacity, anthropometric measurements, hemodynamic assessment, habitual physical activity, and health-related quality of life. Blood and saliva samples are collected for cytokine and antibody biomarker analysis related to SARS-CoV immunity. Pre- and post-intervention evaluations for both groups will be conducted, with the hypothesis that MCE will yield more favorable responses compared to BCI. The study's holistic approach, including the assessment of feasibility, safety, and sustainability, aims to contribute to achieving Sustainable Development Goals (SDG) 3 and SDG 9 b y promoting accessible and sustainable healthcare initiatives for older individuals. This research aligns with global efforts to enhance health and well-being, emphasizing the importance of regular exercise in the aging population.

## Introduction

1

The global aging of the population has been increasing considerably and progressively, which can be attributed to a rise in life expectancy, declining birth rates, improved control of infectious diseases (through immunization), and chronic-degenerative conditions [1]. In the Brazilian population, aging follows the global trend and bears implications for public health [2].

A higher incidence and prevalence of non-communicable chronic diseases (NCDs) have been recorded among the older population, including cardiovascular diseases, diabetes, respiratory diseases, and cancer [3]. These NCDs are the leading cause of morbidity and mortality in the country, and they are largely associated with lifestyle habits such as smoking, physical inactivity (PA), and high-calorie diets [4]. This concerning global scenario demands the integration of public policies for the prevention and control of NCDs, which are based on the adoption of an active lifestyle [5].

Aging is a risk factor NCDs [6], and the literature consistently describes the effects of disease accumulation on health, including musculoskeletal dysfunction, resulting in a reduction in functional capacity [7]. This is accompanied by reductions in physical fitness, such as grip strength, endurance, and muscular strength [8] and a decrease in the ability to sustain exercise or engage in moderate to vigorous PA in advanced ages in a sustainable manner [9]. In turn, compromises in physical health are associated with an increase in sedentary behavior, reduced levels of PA (LPA), and a higher incidence of NCDs, creating a feedback loop [10]. On the other hand, recent evidence has revealed that physically active older adults exhibit higher levels of physical performance, lower risk of NCD accumulation, early hospitalization, and mortality [11].

The decrease in LPA has been associated with a decline in metabolic and immune health in older adults, which can have a negative impact on mental health [12]. Recent studies have consistently reported that low LPA can lead to increased adiposity, insulin resistance, and chronic inflammation [13], all of which are directly linked to the development of metabolic diseases and contribute to oxidative stress in the body [14], which can negatively affect the immune system [15,16]. On the other hand, investigations have demonstrated that regular physical exercise is associated with improved metabolic and immune health and it is considered a “gold standard” treatment for the prevention, mitigation, and management of mental health conditions such as depression and anxiety [17].

In Brazil, assessments of the national public health surveillance system (VIGITEL) between 2011 and 2016 found no significant increases in leisure-time PA, and reported that only 22 % of adults aged 65 years or older met the recommended LPA [18,19]. It is evident that LPA decrease with age, confirming that older Brazilians are a vulnerable group to physical inactivity and NCDs [20,21]. Adding to this, the recent COVID-19 pandemic has imposed significant social changes that have affected people's lifestyles and behaviors, especially among the older population [22]. During lockdown measures, older individuals with NCDs increased their sedentary time and decreased the minutes of walking or other moderate PA per week [23].

Structured exercise programs for groups with a community-based approach have proven to be an excellent way to increase activity levels and physical fitness among the older population [24]. The literature suggests that supervised and structured exercise programs provide more efficient health benefits for older adults compared to unsupervised [25]. However, studies have shown a progressive decrease in adherence to exercise programs over time [26]. This decline in adherence is associated with multiple barriers identified in previous literature, including age, location (or region), gender, socioeconomic conditions, and individual perception (i.e., pleasure, satisfaction, enjoyment), which vary among the population [27].

Recently, there has been discussion about the most effective strategies to increase adherence and reduce barriers to regular exercise in programs targeting geriatric populations, aiming to ensure the sustainability of PA programs [28]. Achieving sustainability in PA programs is a crucial challenge for promoting health in geriatric populations [29]. Several theoretical models are currently utilized to assess the effectiveness and sustainability of public health interventions, including PA programs [30,31]. One example is the RE-AIM model, which encompasses five dimensions: reach, efficacy, adoption, implementation, and maintenance [32]. Recent studies have demonstrated the efficacy of the RE-AIM model in assessing and improving the sustainability of PA programs for geriatric populations, and it has even been used as a tool to develop interventions in the field of PA that can be successfully implemented in real-world settings [33].

The adoption of the RE-AIM model can assist in identifying the strengths and weaknesses of physical activity programs and inform strategies to enhance their sustainability [32]. Recognizing the need for the implementation of public policies targeting populations with low LPA, it is essential to consider intersections such as gender, economic status, and racial identity, acknowledging the social inequality surrounding physical exercise practices in Brazil [34]. Furthermore, the adoption of the RE-AIM model to evaluate the sustainability of PA programs for older adults is of paramount importance in achieving the Sustainable Development Goals (SDGs) set forth by the United Nations [35]. By identifying strengths and comprehending the programs, it becomes possible to develop strategies to improve their sustainability, ensuring that the promotion of physical activity is effective and enduring [36].

The Intervention Study Protocol in Older Health (EISI-SP) aims to implement a physical exercise program for users of the Family Health Strategy in the municipality of Jequié, Bahia, Brazil, with the purpose of increasing LPA in the local population. As a secondary objective, this program will be assessed using the RE-AIM model to determine its feasibility and sustainability for large-scale implementation. Furthermore, at the end of the program, which will span 8 weeks of intervention with a multicomponent exercise and behavioral change approaches, the impact on several metabolic, immune, functional physical fitness, psychological well-being, and mental health indicators will be evaluated.

## Methods

2

### Study design

2.1

The EISI-SP will be a community intervention study, using a non-randomized controlled (nRCT), and short-term pathway model lasting 8–10 weeks [37], with two arms comprised physical exercise group versus control group with lifestyle behavioral change intervention. A pre- and post-design will be employed to assess the impact of the EISI program on several physical, metabolic, cognitive, and immunological function variables in the quantitative analysis. Additionally, a mix method of qualitative-quantitative approach will be conducted to evaluate the components of the RE-AIM model. This study protocol was developed based on the SPIRIT guidelines too [38].

### Ethical statement

The EISI-SP has been approved by the Ethical Committee of the State University of Southwest Bahia with CAEE code 60974222.2.0000.0055. This study protocol adhered to the Brazilian Resolution (466/2012) of the National Council of Health on ethics in research with human participants [39], followed the guidelines for ethics in scientific experiments in exercise science research [40], and complied with the guidelines for research with human subjects of the Helsinki Declaration [41].

### - Eligibility criteria for participants

2.2

Fig. 1 indicating the steps of the study implementation. Individuals registered in the Family Health Strategy (FHS) of the urban area of Jequié-Bahia, Brazil, were invited to participate in the study. Potential participants met the following inclusion criteria: a) not participating in structured physical exercise programs; b) physically independent (able to move independently); c) aged 60 years or older; d) of both genders; e) no diagnosis of SARS-CoV-2 virus within the last 3 months; f) absence of cognitive impairment recorded in medical records; g) completed COVID-19 vaccination strategy. The following exclusion criteria were applied: a) uncontrolled hypertension; b) acute or severe heart failure; c) acute or severe respiratory failure; d) uncontrolled postural hypotension; e) decompensated or uncontrolled diabetes mellitus; f) recent fractures; g) cognitive impairments that could affect test performance; h) any other condition that hinders the completion of physical activity. All clinical health information will be obtained through consultation with the available health records in the ESF.

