### Assessments

2.4

This evaluation phase involves initiating contact with the medical staff of the Family Health Strategy (FHS) to acquire pertinent information regarding participants' medical history and current health, factors that may impact their engagement in the exercise programs. To conduct the initial assessments, a standardized data collection instrument was employed. Participants completed this instrument two weeks prior to the program's commencement and one week following its conclusion. The comprehensive data collection instrument comprised eight sections, encompassing: a) socioeconomic and demographic information; b) lifestyle habits; c) physical-functional status; d) health status questionnaire; e) mental well-being and quality of life; f) questionnaire on Covid-19 infections; g) anthropometric measurements; h) fall risk assessment; and i) feasibility and sustainability of interventions. Application of these questionnaires during this phase was carried out by a team consisting of undergraduate and postgraduate students, physical education professionals, and university professors.

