#### Blood samples

2.5.2

Blood samples will be collected via venipuncture, while the participants are fasting, by a nurse, using appropriate tubes to obtain serum and/or plasma aliquots (minimum of 500 μL). The tubes will be centrifuged at 2500 rpm for 10 min at 4 °C to separate coagulated from non-coagulated blood [67]. The obtained aliquots will then be frozen at −80 °C until subsequent analysis and determination of serum markers. For the determination of cytokines (i.e. IL-6, IL-10, and TNF-alpha), concentrations will be measured in the previously stored serum and saliva at −80 °C using ELISA kits (R&D Bioscience, USA) [69], following the manufacturer's recommendations. To determine specific Immunoglobulins (IgA, IgM, and IgG) for the SARS-CoV-2 virus, concentrations will be measured in the serum and saliva samples using the “in-house” ELISA technique, adapted from the protocol described in previous studies [70].

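### Participants may enter at any time since their last COVID-19 vaccine dose, and the SARS-CoV-2 antibody comparison between non-randomised arms does not adjust for that time

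*Protocol article*

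**What the plan says.** Section 2.2 (Eligibility criteria) lists two COVID-19 conditions for entry. For infection there is a time window: "e) no diagnosis of SARS-CoV-2 virus within the last 3 months". For vaccination there is none: "g) completed COVID-19 vaccination strategy". The same section says that clinical health information comes from the health units' records.

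Section 2.5.2 (Blood samples) makes the virus-specific antibodies an outcome: "To determine specific Immunoglobulins (IgA, IgM, and IgG) for the SARS-CoV-2 virus, concentrations will be measured in the serum and saliva samples". The abstract names the immune response to the virus among the impacts to be assessed.

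Section 2.1 (Study design) describes two arms "using a non-randomized controlled (nRCT), and short-term pathway model lasting 8–10 weeks" and says that "A pre- and post-design will be employed to assess the impact of the EISI program", with immunological function among the variables. Section 2.9 compares the exercise arm (MEP) with the health-education arm (HEP) by an independent-samples t-test or a Wilcoxon test, depending on the distribution, and turns changes into standardised effect sizes. The only covariate named anywhere is session attendance, for secondary analysis (2.6.3).

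The COVID-19 item in the data collection instrument (2.4) is "f) questionnaire on Covid-19 infections". The date of the last vaccine dose is not mentioned, and neither is a dose given between the two assessments.

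**The concern.** A vaccine dose is meant to raise the antibodies that this study measures. Time since the last dose therefore bears on both the baseline level and its later course, whatever the programme does. Criterion g makes vaccination universal in the sample but leaves its timing open, so a participant dosed shortly before baseline and one dosed long before can both enter.

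Randomisation would balance time since dose on average. This study is not randomised, the stated test does not adjust for it, and the date is not among the listed data. What is at stake is how the virus-specific IgA, IgM and IgG results are read: the contrast between arms if recent dosing is unequal, and the change within each arm in any case. Physical activity, function, cognition, quality of life and feasibility are outside the point.

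**Working it through.** The plan states no figure for this, so there is nothing to reproduce. The check gauges how the problem behaves under stated assumptions.

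**Inputs from the article**
- Minimum of 20 per arm; 24 after the adherence allowance (2.2).
- Assessment timing: "Participants completed this instrument two weeks prior to the program's commencement and one week following its conclusion" (2.4). This is stated for the questionnaire instrument; that blood and saliva follow it is an assumption.
- Programme length of 8–10 weeks (2.1, 2.6).

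**Interval between samples**
- 2 + 8 + 1 = 11 weeks to 2 + 10 + 1 = 13 weeks, that is 77 to 91 days.
- The article also gives 16 weeks (abstract) and 4 months (2.6.1). With 16 weeks the interval is 2 + 16 + 1 = 19 weeks.

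**Assumed, not in the documents**
- q1 and q0: the share recently dosed in each arm.
- D: the extra antibody change in recently dosed participants, in SDs of change among the others.

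**Formulas**
- Between-arm bias = (q1 − q0) × D.
- Within-arm bias = q × D.
- Variance of change, relative to no recent dosing = 1 + q(1 − q)D².

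**Simulation**: 20 per arm, no programme effect, normal changes, two-sided 5% level, 20,000 repetitions. The within-arm column tests the first arm's mean change against zero.

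| q1 / q0 | D | Between-arm bias (SD) | False positives between arms | False positives within first arm |
|---|---|---|---|---|
| 0 / 0 | 1 or 2 | 0 | about 5% | about 5% |
| 20% / 20% | 1 | 0 | 5% | 12% |
| 20% / 20% | 2 | 0 | 5% | 25% |
| 30% / 10% | 1 | 0.2 × 1 = 0.2 | 9% | 21% |
| 30% / 10% | 2 | 0.2 × 2 = 0.4 | 16% | 46% |
| 50% / 10% | 1 | 0.4 × 1 = 0.4 | 21% | 47% |
| 50% / 10% | 2 | 0.4 × 2 = 0.8 | 47% | 85% |

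**Variance in the balanced case, q = 20%**
- D = 1: 1 + 0.2 × 0.8 × 1 = 1.16, so the standard error rises by a factor √1.16 = 1.08.
- D = 2: 1 + 0.2 × 0.8 × 4 = 1.64, a factor √1.64 = 1.28.

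**Would a 3-month exclusion remove the drift?** Assume a half-life H of 30 to 90 days. The fold fall over T days is 2^(T/H): from 2^(77/90) = 1.8 to 2^(91/30) = 8.2. If 6 of 24 (25%) in one arm and none in the other fall in this way while everyone else stays flat, the spurious ratio of geometric means is 2^(−0.25 × T/H) = 0.59 to 0.86. With 25% in both arms it is 2^0 = 1.00. But a constant half-life has no memory. Someone dosed 3 months before baseline falls by the same factor over the next T days, so under that model excluding doses within 3 months removes none of the drift. The exclusion works only if decay also stops at about 3 months, which is a further assumption.

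**The case against.** - **The concurrent control arm.** A reader might infer that any post-vaccine rise or fall will be analysed as a programme effect. The documents do not support this for the main comparison. Section 2.9 sets MEP against a concurrent HEP arm, and drift common to both cancels. Bias between arms needs unequal recent dosing; non-random allocation permits that, but nothing in the article shows it. This objection stands for the between-arm contrast. It does not cover within-arm change, which the pre-post design and the effect sizes from changes invite.
- **Inconsistency with the infection window.** A reader might infer that the plan accepts that recent antigen exposure disturbs the immune outcomes and then forgets vaccination. The article gives no reason for criterion e, which could equally concern safety or fitness to exercise. Nor does anything suggest that criterion g prompts people to be vaccinated in order to qualify.
- **The SAP or full protocol may adjust.** Covariates are often left there. The entry criteria and the main comparison are stated in this article, however, and both leave time since dose open.
- **Scope.** The stated main aim is to raise physical activity. The antibodies are one set among many outcomes. This stands and limits the weight of the point.

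**Conclusion.** The point holds in a limited form. As written, the plan leaves time since the last vaccine dose uncontrolled in the SARS-CoV-2 antibody outcomes. With unequal recent dosing, the between-arm contrast is biased. With equal recent dosing, it is not; what remains is distorted within-arm change and added variance.

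The size cannot be stated, because the documents give neither the share recently dosed nor the antibody kinetics. The illustrative false-positive rates rest on assumed shares and an assumed shift of 1 to 2 SD. The 11–13 week interval borrows the questionnaire timing and one of several programme lengths in the article.

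A reader might go further and conclude that entry needs a 3-month vaccine wash-out. The documents do not support that: they give no kinetics from which to set a window, and under constant decay a window would not help. This is a worthwhile, low-cost improvement for one group of outcomes and does not threaten the study's main aims.

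**What to change.** 1. Record the date of the last COVID-19 vaccine dose, and any dose or infection up to the post-programme sample, from the health records (2.2) and the COVID-19 questionnaire (2.4) already in use.
2. In 2.9, for the SARS-CoV-2 antibody outcomes only, replace the unadjusted test with a regression of the post value on arm, baseline value and time since last antigen exposure (dose or infection), with antibody values on the log scale. Doses or infections between the two samples occur after allocation, so tabulate them by arm and say beforehand how they enter the model.
3. Report time since last dose by arm at baseline, and do not read within-arm antibody changes as programme effects.
4. Use exclusion of participants dosed within 3 months at most as a sensitivity analysis, not as an entry rule. If 6 of 24 were excluded, 24 − 6 = 18 would remain, below the plan's minimum of 20 per arm.

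The cost is one extra data item per participant and about one degree of freedom for the time-since-exposure term, with 20–24 per arm. Eligibility, the interventions and all other outcomes stay as they are.

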**Fig. 1 fig1:**
[figure not shown]
**–** Timeline of the EISI study implementation.

A minimum sample size of 20 participants per group will be recruited, which is sufficient to detect significant changes considering a statistical effect size of p = 0.05, as established take into account previous similar study [42]. However, considering a predicted adherence rate of 70 % to the program, a minimum sample size of n = 24 for both the intervention and control groups is justified.

### Precautions

2.3

The exercise sessions' instructor did not participate in data collection procedures. Trained research personnel conducted the collection of saliva, blood, and global health assessments. The principal investigators organized the assessment of psychometric and cognitive scales, as well as the physical-functional fitness battery, which was administered by specialists and co-investigators of the research team. To minimize procedural differences, the same evaluators performed data collection, completed both baseline and follow-up questionnaires, and conducted the physical-functional fitness battery tests. To accommodate participants who face difficulties in moving outside of their neighborhood for study participation, the classes will be conducted in suitable spaces within the Family Health Units (USFs).

### Assessments

2.4

This evaluation phase involves initiating contact with the medical staff of the Family Health Strategy (FHS) to acquire pertinent information regarding participants' medical history and current health, factors that may impact their engagement in the exercise programs. To conduct the initial assessments, a standardized data collection instrument was employed. Participants completed this instrument two weeks prior to the program's commencement and one week following its conclusion. The comprehensive data collection instrument comprised eight sections, encompassing: a) socioeconomic and demographic information; b) lifestyle habits; c) physical-functional status; d) health status questionnaire; e) mental well-being and quality of life; f) questionnaire on Covid-19 infections; g) anthropometric measurements; h) fall risk assessment; and i) feasibility and sustainability of interventions. Application of these questionnaires during this phase was carried out by a team consisting of undergraduate and postgraduate students, physical education professionals, and university professors.

